### Participant timeline

The enrollments of the two allocation groups take place in two consecutive enrollment periods. Every period lasts one year starting with the control group.

The patients express interest to participate in the supply concept to the enrollment person who reviews the inclusion and exclusion criteria. Furthermore, the enrollment person informs and educates the patient and hands over the oncological ring folder. After successful enrollment a standardized form is sent to the statutory health insurance company and to the evaluator. This informs the evaluator about the patient assignment and the agreement to establish contact (e.g. by telephone).

From this point in timeline there are small differences between the two groups in collecting the baseline data.

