**Methods:**

The study population includes all cancer types, both new and existing diseases. PIKKO (with patient navigator, oncological knowledge database, specialized oncological counseling) is evaluated within a controlled, non-randomized, comparative, multicenter, longitudinal design. In addition to patient surveys, data from statutory health insurances and utilization data from the web database are collected, and interviews with patient navigators and doctors are carried out. Patients are assigned to a control (usual care) or an intervention group (u. c. + PIKKO). Primary outcome is the health related quality of life (SF-12) six months after baseline. Secondary outcomes are self-efficacy (GSE), psychological distress such as depression (PHQ-9) or anxiety (GAD-7), health literacy (HLS-EU-Q47) and patient satisfaction in health care (Qualiskope-A). Furthermore, the time course of direct costs of medical care (e.g. work disability days) and usage data of the intervention modules are analyzed. Among other statistical procedures, we use t-tests, univariate tests and growth curve models.

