## Methods / design

### Objectives

PIKKO focuses on communicative aspects and informative needs of cancer patients and consists of four modules. The patients receive (1) the advice of a trained PN and (2) an access to a new database with evidence based information about cancer. Furthermore a fast access to a specialized oncological counseling is guaranteed (3). Finally, a ring folder is provided to patients to cope the paper flood during their illness (4). Within the project the new consulting and information path (treatment as usual plus PIKKO) is integrated to usual care (Fig. 1).

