The forth module of the intervention was also created by the German Cancer Society. It is a ring folder, which is given to all patients at the time of their agreement. With this folder patients can collect and organize all information concerning physician or any other consulting contacts, to keep a personal medication list, to document physical complaints and to collect any discharge letter in a structured way. This folder is not only intended to improve the self-management capabilities of patients, but also to minimize informational deficits in the case of a change of care providers. In this way, patients can find other specialists and hand them over their entire treatment documentation as needed.

For any participating physician a hotline of oncologists was established. The hotline is called “onco-expert-phone” and provides the physicians fast and anytime with unbureaucratic help in case of treatment issues.

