#### Intervention group

In the intervention group it has to be ensured that the baseline survey is carried out before the intervention starts. Due to the lack of time, the baseline questionnaire is issued directly by the PN. Before the patient and the PN start with the consultation the patient fills out the written baseline questionnaire (rated as consent to the survey). The consultation starts after the handing over of the baseline questionnaire to the PN. In addition to various consulting content and during the first consultation the PN unlocks the patient access to “Mein PIKKO” and offers the specialized oncological counseling. Later the PN returns the patient-filled questionnaire postage free to the evaluator.

In both groups the dates of the following questionnaires are computed dependent on the filling date of baseline, which is gathered directly after inclusion (T0). The patients are contacted to fill out questionnaires three (T1), six (T2), nine (T3) and twelve months (T4) after baseline, unless the patient withdraws the consent or dies, or changed from control to intervention group.

Baseline, main outcome and every follow-up survey consist of a set of questionnaires (see Table 1).

**Table 1 Tab1:** Directly measured patient outcomes and time of measurement

Measure	Source	T0	T1	T2	T3	T4
Demographics	Control + intervention group	X	X			
Demographics, reduced	Control + intervention group			X	X	X
Social burden	Control + intervention group	X	X			
Social support	Control + intervention group	X	X	X	X	X
Cancer, status and treatment	Control + intervention group	X	X			
Cancer, changes	Control + intervention group		X	X	X	X
Chronic diseases	Control + intervention group	X	X			
Health-related quality of life (SF-12)	Control + intervention group	X	X	X	X	X
Self-efficacy (GSES)	Control + intervention group	X	X	X	X	X
Depression (PHQ-9)	Control + intervention group	X	X	X	X	X
Anxiety (GAD-7)	Control + intervention group	X	X	X	X	X
Patient satisfaction in health care (Qualiskope-A)	Control + intervention group	X	X	X	X	X
Health literacy (HLS-EU-Q47)	Control + intervention group	X	X	X	X	X
Nutrition	Control + intervention group	X	X	X	X	X
Alcohol use and smoking	Control + intervention group	X	X	X	X	X
Intervention modules						
Use of oncological ring folder	Control + intervention group		X	X	X	X
Utilization of PN	Intervention group		X	X	X	X
Utilization of specialized oncological counseling	Intervention group		X	X	X	X

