### Strengths

This new supportive care concept is intended to establish an offer for all cancer patients. Low barriers for the procurement of information such as the website, which offers both specific and general information, are just as much a part of the concept as the broad further training of PN, who can thus advise all cancer patients.

The study is designed to evaluate the effect of PIKKO interventions under naturalistic conditions. The according heterogeneity of the sample (age range, all cancer types, all sexes) tries to reflect the reality of oncological care. Due to the heterogeneity of the sample, subgroup analyses are planned to show which module of PIKKO works best for whom.

Furthermore, the longitudinal design with five measurement points allows the investigation of long-term effects.

Last, the telephone interviews with participating PN and physicians can show experiences in the implementation that help to make PIKKO a common part of cancer care.

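### Controls also receive the ring folder, PIKKO's fourth module, so the questionnaire outcomes test the other three modules added to usual care plus folder, and the design cannot show which module works best.

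*Protocol article*

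**What the plan says.** Several parts of the Protocol article describe the ring folder as part of PIKKO and as given to everyone:

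- Objectives: "PIKKO focuses on communicative aspects and informative needs of cancer patients and consists of four modules". These are the navigator, the database, the counselling and the folder.
- Intervention, on the fourth module: "It is a ring folder, which is given to all patients at the time of their agreement". The folder is meant to strengthen self-management and to limit information loss when a patient changes provider.
- Participant timeline, in text that applies to both groups: "the enrollment person informs and educates the patient and hands over the oncological ring folder". Only after this does the section say "From this point in timeline there are small differences between the two groups in collecting the baseline data".
- Table 1: the row "Use of oncological ring folder" stands in the block on intervention modules and names control and intervention group as its source, at T1 to T4. Every other row of that block names the intervention group alone.

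Other parts describe a control without PIKKO. The Abstract says "Patients are assigned to a control (usual care) or an intervention group (u. c. + PIKKO", and its own list of components has the navigator, database and counselling but no folder. Trial design calls the first control group treatment as usual. Primary outcome contrasts treated patients with patients who have no intervention.

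Two further statements matter. The subsection Intervention group says "In the intervention group it has to be ensured that the baseline survey is carried out before the intervention starts". The Strengths section says "subgroup analyses are planned to show which module of PIKKO works best for whom".

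**The concern.** A control group that holds one of the four defined modules is not a usual-care group. The effect on quality of life, self-efficacy, distress, health literacy and satisfaction would then be reported for a package and a comparator that were not the ones compared. The Abstract's Discussion foresees a national roll-out and entry into guidelines, so it matters which package the estimate belongs to. The folder cannot be set aside as inert either, because the article gives it a purpose that overlaps with outcomes it measures.

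The module question is related. To say which module works best, the design needs variation in each module that does not come from the patient's own choice. Nothing in the article supplies that variation.

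**Working it through.** **1. What each questionnaire group receives**

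| Component | Control | Intervention | Source |
|---|---|---|---|
| Usual care | yes | yes | Trial design |
| Ring folder | yes, at enrolment | yes, at enrolment | Intervention; Participant timeline; Table 1 |
| Navigator | no | yes | Intervention group; Table 1 |
| Database | no | yes | Intervention group; Table 1 |
| Counselling | no | offered | Intervention; Intervention group; Table 1 |

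The sentence in Participant timeline does not itself name the controls. The words on all patients in the Intervention section and the source column of Table 1 settle the point.

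**2. The contrast**

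Let U be the expected outcome under usual care, F under usual care plus folder, and P under usual care plus all four modules.

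- Four-module effect: P − U = (P − F) + (F − U)
- Contrast delivered by the questionnaires: P − F = (P − U) − (F − U)

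If the folder alone helps (F better than U), P − F is smaller than P − U. If it does nothing, the two are equal. This concerns only the target quantity. Bias from the non-randomised, sequential recruitment is a separate matter.

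**3. Timing**

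The folder is handed over at enrolment. T0 follows: by post after a telephone call in the control group, and at the first navigator visit in the intervention group. Baseline therefore precedes navigator, database and counselling, but not the folder, in either group. For one of its four modules the article does not meet its own requirement.

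**4. Sample size as planned**

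Inputs from Sample size calculation: d = 0.25, two-sided α = 0.05, power 0.90, equal groups, 33.3% dropout.

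- Normal approximation: n = 2(1.960 + 1.282)²/0.25², which rounds up to 337 per group. The t-test calculation gives 337.2, so 338. Reproduced.
- Dropout: 338/(1 − 1/3) = 507 per group and 676/(1 − 1/3) = 1014 in total. Reproduced.
- Power at 338 per group: noncentrality = d·√(338/2) = 13d = 3.25, and Φ(3.25 − 1.96) = 0.90.

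**5. Power if part of d belongs to the folder**

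The article gives no effect for the folder. Let s be the share of d = 0.25 that the folder carries. Both the share and the reading of d are assumptions.

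| Reading of d = 0.25 | s | Contrast 0.25(1 − s) | 13 × contrast | Power |
|---|---|---|---|---|
| Difference between the groups as constituted | 0 | 0.25 | 3.25 | 0.90 |
| Four-module effect | 10% | 0.225 | 2.925 | 0.83 |
| Four-module effect | 20% | 0.20 | 2.60 | 0.74 |

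**6. The module claim**

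- Folder: both questionnaire groups have it, so there is no folder-free questionnaire comparison.
- Navigator, database, counselling: these arrive together. Counselling is an offer, and the database is used at will once access is unlocked.
- Use of these three is recorded only in the intervention group and only from T1, so groups of users are formed after baseline by the patients themselves.
- The propensity score in Statistical methods addresses differences between control and intervention group, not who uses which module.

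**The case against.** The strongest reply is that this is a labelling fault. The Abstract describes PIKKO by navigator, database and counselling, and that is the increment the design delivers. The navigator is called the central module, and baseline does precede these three. A helpful folder in both groups pulls the contrast towards the null relative to the full package, so it cannot produce a spurious benefit. All of this stands. A reader might infer that nothing can be concluded about PIKKO against usual care; the documents do not support that, because the three-module increment is still estimable.

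A reader might also infer that the trial is underpowered. Sample size calculation ties d = 0.25 to the t-test on the primary outcome, and Primary outcome describes that as a comparison of the group means. On that reading nothing is lost.

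Third, Trial design and Additional data describe a second control group outside PIKKO with insurance data. For costs and days of inability to work, a group without the folder therefore exists, although its stated purpose is to examine representativeness and compare treatment courses. The point must be confined to the questionnaire outcomes.

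Fourth, Statistical methods plans subgroup analyses for conditional treatment effects, which baseline-defined subgroups would satisfy, and no comparison of users with non-users is described. That is fair, but the Strengths section promises a result by module, and no choice of subgroups within this design can deliver it. A reader might go further and suppose that needier patients use more modules, so that a module would look harmful. The article does not say so. Its remarks on selection, in Limitations, concern participation and point towards less burdened and more motivated patients. The direction of confounding is unknown.

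**Conclusion.** The point holds, limited to the primary and other questionnaire outcomes. The control is usual care plus ring folder, which contradicts the Abstract, Trial design and Primary outcome. The contrast tested is navigator, database and counselling on top of that. It is a valid target; if the folder helps, it understates the four-module effect.

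The cost in power ranges from none, if d = 0.25 is the difference between the groups as constituted, to a fall from 0.90 to about 0.83 or 0.74, if d is the four-module effect and the folder carries 10% or 20% of it. The article fixes neither the reading nor the share, so this is an illustration and not a finding of inadequate power.

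The claim to show which module works best is not supported, and its possible bias cannot be sized or signed from the article.

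**What to change.** 1. Reconcile Abstract, Objectives, Trial design, Intervention, Primary outcome, Participant timeline and Intervention group. State the comparator as usual care plus ring folder, and the estimand as the increment from navigator, database and counselling. Say that T0 precedes those three but follows the folder.
2. State which contrast d = 0.25 refers to.
3. Make no effect claim for the folder on questionnaire outcomes.
4. Limit effect-modification analyses to subgroups defined at baseline, with group-by-subgroup interaction tests.
5. Report module use and ratings descriptively within the intervention group, or label any link with outcome as an exploratory association.
6. Withdraw the module-effect claim from Strengths.

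The cost is wording and a narrower claim. No new data are needed, and the data collection and sample size stay as they are.

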#### Control group

The evaluation team contacts the patient per telephone and informs the patient about the process of the patient survey (consent to the survey). Then the written baseline questionnaire will be sent to the patient. The patient returns the completed questionnaire postage free to the evaluator.

#### Intervention group

In the intervention group it has to be ensured that the baseline survey is carried out before the intervention starts. Due to the lack of time, the baseline questionnaire is issued directly by the PN. Before the patient and the PN start with the consultation the patient fills out the written baseline questionnaire (rated as consent to the survey). The consultation starts after the handing over of the baseline questionnaire to the PN. In addition to various consulting content and during the first consultation the PN unlocks the patient access to “Mein PIKKO” and offers the specialized oncological counseling. Later the PN returns the patient-filled questionnaire postage free to the evaluator.

In both groups the dates of the following questionnaires are computed dependent on the filling date of baseline, which is gathered directly after inclusion (T0). The patients are contacted to fill out questionnaires three (T1), six (T2), nine (T3) and twelve months (T4) after baseline, unless the patient withdraws the consent or dies, or changed from control to intervention group.

Baseline, main outcome and every follow-up survey consist of a set of questionnaires (see Table 1).

**Table 1 Tab1:** Directly measured patient outcomes and time of measurement

Measure	Source	T0	T1	T2	T3	T4
Demographics	Control + intervention group	X	X			
Demographics, reduced	Control + intervention group			X	X	X
Social burden	Control + intervention group	X	X			
Social support	Control + intervention group	X	X	X	X	X
Cancer, status and treatment	Control + intervention group	X	X			
Cancer, changes	Control + intervention group		X	X	X	X
Chronic diseases	Control + intervention group	X	X			
Health-related quality of life (SF-12)	Control + intervention group	X	X	X	X	X
Self-efficacy (GSES)	Control + intervention group	X	X	X	X	X
Depression (PHQ-9)	Control + intervention group	X	X	X	X	X
Anxiety (GAD-7)	Control + intervention group	X	X	X	X	X
Patient satisfaction in health care (Qualiskope-A)	Control + intervention group	X	X	X	X	X
Health literacy (HLS-EU-Q47)	Control + intervention group	X	X	X	X	X
Nutrition	Control + intervention group	X	X	X	X	X
Alcohol use and smoking	Control + intervention group	X	X	X	X	X
Intervention modules						
Use of oncological ring folder	Control + intervention group		X	X	X	X
Utilization of PN	Intervention group		X	X	X	X
Utilization of specialized oncological counseling	Intervention group		X	X	X	X
Utilization of psychological consultation	Intervention group		X	X	X	X
Use of oncological knowledge database	Intervention group		X	X	X	X
Rating the intervention	Intervention group		X	X	X	X

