### Outcomes

#### Primary outcome

The primary outcome is the health-related quality of life (HRQoL) particularly the mental component score measured by the SF-12 questionnaire [28, 29] six months after baseline. Patients underwent intervention are supposed to improve their psychological QoL to a greater extent than patients without intervention (comparison of means of study groups). SF-12 is the valid and tested short form of the SF-36 questionnaire [30]. It is used in many cases of cancer research (e.g. [31, 32]). HRQoL is based on self-report questionnaires filled out by the patients themselves.

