### Sample size calculation

The three participating health insurance companies have a potential of 325,000 insured persons in the Saarland and their averaged prevalence of cancer (ICD-10-diagnosis groups C00-C97 or D45-D48) is 6.532%. Thus, the study population included (rounded up) 22,000 patients.

The financing of the PIKKO supply concept was calculated for a maximum of 1.800 patients per group, 3.600 patients in total. That means that 1.800 participants of the intervention group can benefit from the PN and the other intervention modules.

To evaluate the PIKKO intervention only 676 participants (338 per group) of the patient questionnaires are required to the statistical analyses. This number of cases was calculated with the program GPower version 3.1.7 [41]. The calculation is based on an expected effect of d = 0.25 for a two-sided t-test with same sized comparative groups, a level of significance of α = 0.05 and a power of 1-β = 0.9. The t-test refers to the primary outcome. We assumed that 338 patients would drop out and added this amount to the total number of included patients. As a consequence, the recruiting aim was *N* = 1014 = 676 + 338 patients (per group 507 = 338 reaching the end point + 169 dropout). The expected dropout rate was 33.3% regarding the baseline (338 of 1014) or respectively 50% regarding the patients reached the endpoint (338 of 676).

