### Statistical methods

Characteristics of control and intervention groups (e.g. age, sex, education, family situation, partner situation) will be analyzed with descriptive statistics. Since no randomization is made for ethical and research practical reasons, univariate tests are used to determine which of the above mentioned characteristics differ between the two groups. Ideally there are no significant differences between the two groups. In the case of significant differences we will compute propensity scores using the corresponding pre-treatment variables. Then, we will apply in the subsequent analyses propensity scores as stabilized regression weights to reduce bias caused by different group characteristics.

The main hypothesis of an intervention effect on psychological and physical health, self-efficacy, health care costs etc. will be proofed by the comparison of averages of intervention and control group (resp. t-tests). To estimate the corresponding regression adjusted group means we will use growth curve models. Furthermore, we will conduct subgroup analyses to identify conditional treatment effects.

For dropout analysis we will conduct a logistic regression with dropout as criterion and group assignment and baseline variables as predictors applying the regression weight mentioned above. For the time-to-event analysis we will conduct a Cox regression.

The level of significance will be α = 0.05. To validate our analyses, we will conduct the analyses with imputed missing data and without imputation.

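### The two groups enter the questionnaire evaluation by different routes (controls by telephone and post, intervention patients only at a first navigator consultation), and no planned analysis accounts for patients lost before T0

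*Protocol article*

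**What the plan says.** Up to the enrolment form, both groups follow the same path (Protocol article, Participant timeline). That section then announces: "From this point in timeline there are small differences between the two groups in collecting the baseline data".

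- **Controls** (section Control group): the evaluation team telephones the patient and obtains consent to the survey. "Then the written baseline questionnaire will be sent to the patient", and it goes back by post to the evaluator.
- **Intervention patients** (section Intervention group): "Due to the lack of time, the baseline questionnaire is issued directly by the PN". The patient completes it before the first consultation begins, completion is treated as survey consent, and the navigator collects it and forwards it later. No other route to T0 is described.
- **Both groups**: "In both groups the dates of the following questionnaires are computed dependent on the filling date of baseline, which is gathered directly after inclusion (T0"). T1 to T4 are scheduled from that date.

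The primary outcome is health-related quality of life, "particularly the mental component score measured by the SF-12 questionnaire", six months after baseline (T2). The expectation is that "Patients underwent intervention are supposed to improve their psychological QoL to a greater extent than patients without intervention". Group means are compared by t-test, and the sample size rests on an "expected effect of d = 0.25 for a two-sided t-test with same sized comparative groups".

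**The concern.** As written, an enrolled intervention patient without a navigator contact has no T0, no survey consent and no follow-up dates, and so does not appear in the SF-12 comparison. A control needs no navigator visit but must be reached by telephone, agree, and return a long postal form. The people analysed in the two groups have therefore passed different tests, and a difference in T2 means may partly reflect that.

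T0 itself also differs: it is issued and collected by the future care provider in one group and exchanged by post with the evaluator in the other. Any analysis that uses T0 inherits that difference.

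At stake is the reading of the primary result. Without an account of who was lost before T0, a modest difference, or its absence, cannot be attributed to the programme with confidence. The insurer outcomes are not exposed in this way, because the Limitations section says those data are collected for all included patients without their direct participation.

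**Working it through.** **1. Can enrolment and the first consultation come apart?** Yes. About 80 physicians in about 25 cities recruit (Study setting), insurers can enrol by post, and up to ten navigators can be trained (Recruitment). The document gives no attendance figure and no enrolment-to-T0 interval.

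**2. Do the planned methods reach people without T0?**

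- Propensity weights (Statistical methods) are computed only if univariate tests show significant differences, and they use pre-treatment variables. They can balance measured characteristics among patients who have T0. They cannot bring back those who do not, and willingness to attend a navigator is not observed in controls.
- Dropout is counted from baseline (Sample size calculation: 338 of 1014), and the dropout regression uses baseline variables. Loss before T0 is outside both.
- Imputation has no questionnaire data to start from for these patients.
- The second control group supplies insurer data only, which cannot be matched to questionnaires (Data collection methods), so it cannot quantify the effect on SF-12.

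**3. The plan's own figure.** Inputs: d = 0.25, two-sided α = 0.05, power 0.90. Normal approximation: n = 2 × (1.960 + 1.282)² / 0.25² = 336.3, rounded up to 337 per group. The noncentral t gives 337.2, rounded up to 338. Total 676; 676 / (1 − 1/3) = 1014. The stated size reproduces. It covers sampling error only.

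**4. Net bias from two filters, in SD units.**

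net bias = q_I × δ_I − q_C × δ_C

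Here q is the share of enrollees lost before T0 in the intervention (I) or control (C) group, and δ is the T2 mean of those retained minus the mean that those lost would have had. None of the four inputs is in the document. If both filters lose the same share with the same δ, the net bias is zero.

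The table is an assumption: 10% to 30% excess loss in one group and a difference of 0.2 to 0.5 SD. The standard error at 338 per group is √(2/338) = 0.0769 SD.

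| Excess loss × difference | Net bias (SD) | Share of d = 0.25 | Two-sided rejection, no true effect | Power at d = 0.25 if bias acts against the intervention |
|---|---|---|---|---|
| 0.10 × 0.2 | 0.02 | 8% | 5.8% | 84.8% |
| 0.10 × 0.5 | 0.05 | 20% | 10.0% | 73.8% |
| 0.20 × 0.5 | 0.10 | 40% | 25.5% | 49.5% |
| 0.30 × 0.5 | 0.15 | 60% | 49.6% | 25.5% |

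Example, third row: 0.10 / 0.0769 = 1.30, and P(Z > 1.96 − 1.30) = P(Z > 0.66) ≈ 0.255.

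**5. Shift in T0 from the different setting.** Assume a shift s of 0.1 to 0.2 SD, of either sign, and a T0-to-T2 slope of 0.5.

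- Unadjusted comparison of T2 means: 0.
- Baseline-adjusted comparison: 0.5 × s = 0.05 to 0.10 SD.
- Change score: s = 0.1 to 0.2 SD.

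Showing T2 with and without T0 adjustment therefore indicates how much the result depends on T0.

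**The case against.** Four stronger readings are tempting, and the document does not support them.

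- **That selection exists in the intervention group only.** A control who is too ill, changes their mind or dies before returning the postal form is lost as well. Only the navigator visit is specific to the intervention group.
- **That the bias must favour the programme.** Patients who skip the navigator because they feel no need might score higher, which would reverse the sign. The percentages above are illustrations, not estimates.
- **That intervention patients answer under observation.** The text says the navigator issues and receives the form, not that the navigator watches or reads it.
- **That intervention T0 is later than control T0, contradicting the statement that it directly follows inclusion.** No interval is given for either group. The reference to lack of time can be read as the first consultation following too quickly for a postal procedure, and the postal control T0 may be the later one.

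It is also fair to say that collecting T0 before the intervention starts is sound, that a T0 setting effect does not enter an unadjusted T2 t-test, and that the hypothesis is already worded for patients who underwent the intervention.

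What remains is the asymmetry itself. It is a stated procedure rather than a detail left to a fuller document, it acts on the primary comparison through who is analysed, and the Limitations section, which discusses voluntary participation and non-randomisation, does not mention it.

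**Conclusion.** The point holds as a difference in entry filter and T0 setting between the groups, described as small and not carried into the limitations or the analysis. That much follows directly from the Participant timeline section and its two group subsections.

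Whether it biases the SF-12 result, by how much and in which direction cannot be determined from the document. The range of 0.02 to 0.15 SD (8% to 60% of d = 0.25) rests wholly on assumed loss and assumed differences, and the net bias could be nil if the two filters happen to balance. The upper part of that range would be enough to produce or hide a significant result, so the numbers lost before T0 are needed before the primary result can be interpreted.

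**What to change.** **Where T0 is still to be collected** (a roll-out or a similar study): use one route in both groups. Issue T0 and the survey consent at enrolment, by post for patients enrolled by post. The form goes back sealed to the evaluator, and the navigator only confirms before the first consultation that it has been completed. Follow all consenting enrollees whether or not they attend. The cost is envelopes, an amended enrolment instruction and a separate consent step. T0 return in the intervention group may be somewhat lower and the effect more diluted, though comparable.

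**For this trial**, where recruitment ended on 31 March 2020 (Trial status):

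1. From the evaluator's database, which records allocation, navigator, and enrolment, dispatch and fill-out dates (Data organization), report per group the numbers enrolled and with T0, the number with navigator contact (intervention), and the enrolment-to-T0 interval.
2. Present the T2 comparison with and without T0 adjustment.
3. Add a sensitivity analysis for loss before T0: put the observed q_I and q_C into the formula above, vary δ_I and δ_C over positive and negative values, and report the values at which the conclusion changes. This is needed even with a restricted conclusion, because the control group still contains patients who would not have attended a navigator.
4. Limit the conclusion on questionnaire outcomes to patients who attended the navigator, and name the different T0 routes as a limitation.

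The cost is a little extra analysis and a narrower, possibly less favourable conclusion.
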